#### Executive function

The Stroop test is a neuropsychological test commonly used to assess the inhibition control component of executive function and test the subject's ability to inhibit cognitive interference that occurs when the processing of the target stimulus feature is impeded by the simultaneous processing of a second stimulus attribute (49).

#### ADHD symptoms and behavior

The ADHD Rating Scale–IV (ADHD RS-IV) (50, 51) is a widely used ADHD scale comprising 18 items. The participant's parent rates the frequency of each symptom on the scale. Each item is scored on a 4-point Likert scale of 0–3 (0: never or rarely; 1: sometimes; 2: often; and 3: very often). The nine odd items evaluate attention deficits, composing the inattention subscale (or IA); the nine even items evaluate hyperactivity-impulsivity, composing the hyperactivity-impulsivity (or HI) subscale; the total score is the sum of all the scores on the 18 items. The ADHD RS-IV is a reliable and valid scale that can be used for the Chinese population (52).

### Neuroimaging

Participants will receive pre- and post-treatment MRI scans (total: two MRI scans) to measure any changes in structural and functional connectivity changes in the brain. Structural MRI, DTI, and rs-fMRI will be performed using a 3T scanner at the UBSN (ZB216), The Hong Kong Polytechnic University. The subjects will be closely monitored by the research assistant and the radiographer during scanning. The whole scan will last around 30 min including preparation. Structural MRI scans including T1 sequences will be used for assessing regional volume differences across the whole brain. High-resolution sagittal 3D T1-weighted (SPGR/MPRAGE) images of 1 × 1 × 1 mm will be acquired with a repetition time (TR) = 1,820 ms, echo time (TE) = 3.75 ms, inversion time (TI) = 1,100 ms, and flip angle = 70°. DTI sequence will be conducted using single-shot spin-echo echo-planar imaging, with diffusion-sensitizing gradients applied along 16 non-collinear directions with diffusion weighting factor b = 1,000 s/mm^2^, plus two b = 0 images. The imaging parameters will be TR/TE = 1,200/82 ms, matrix size = 128 × 128, the field of view (FOV) = 240 mm, slice thickness = 3 mm with no intersection gap, number of excitations = 2, and number of slices = 67. Finally, resting-state fMRI of 150 T2-weighted gradient echo planar imaging (EPI) will be acquired with TR = 2 s and TE = 32 ms; 32 slices, with a resolution of 3 × 3 × 4 mm, during which subjects will view a fixation cross (“+”) passively at the center of the screen. Images processing and analysis will be performed using software packages including FSL (http://fsl.fmrib.ox.ac.uk/fsl/fslwiki/). Total brain and total gray and white matter volumes will be extracted from the T1 structural scan. Gray matter and white matter tissue maps will be segmented and compared for regional tissue density differences using voxel-based morphometry (VBM) (53). Structural connectivity will be assessed by fractional anisotropy (FA) maps extracted from DTI imaging.

For functional connectivity, all resting state-fMRI (rs-fMRI) volumes will be pre-processed, with motion correction and slice timing correction, then linearly registered to the Montreal Neurological Institute (MNI) standard space. A data-driven approach will be used for the analysis of rs-fMRI data. Independent component analysis will be done with Multivariate Exploratory Linear Decomposition in FSL. A set of independent components will be identified as the common resting-state functional networks. The global and local efficiency, modularity, and hubs will be computed using the Brain Connectivity Toolbox (https://sites.google.com/site/bctnet/). A dual regression approach will be used to investigate between-group differences in the individual functional networks. The significance threshold of the voxel-wise differences will be set at *p* < 0.05 (family-wise error corrected).

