### Secondary hypotheses

Participants in the verum TPS group or the sham TPS group will have < 5% somatic discomfort during the 2-week TPS intervention on young adolescents with ADHD.Participants in the verum TPS group will have a 30% improvement in ADHD symptoms and behavior compared with the sham TPS group after 2 weeks of TPS treatment and be maintained at the 1- and 3-month follow-ups.Participants in the verum TPS group will have a 30% improvement in executive function after 2 weeks of TPS treatment compared with the sham TPS group and be maintained at the 1- and 3-month follow-ups.Participants in the verum TPS group will have a 30% improvement in both attention deficit and reduction in hyperactivity and impulsivity after 2 weeks of TPS treatment compared with the sham TPS group, and be maintained at the 1- and 3-month follow-ups.Participants in the verum TPS group will have more brain connectivity changes after 2 weeks of TPS compared with the sham TPS group and be maintained at the 1- and 3-month follow-ups.

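### Motion correction is the only motion step named for the resting-state fMRI, so a between-arm difference in scanner movement would be a rival explanation for a connectivity effect

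*Protocol article*

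**What the plan says.** The Neuroimaging section of the protocol article sets out the resting-state analysis in order. First, "all resting state-fMRI (rs-fMRI) volumes will be pre-processed, with motion correction and slice timing correction, then linearly registered" to standard space. ICA is then run in FSL, and its stated purpose is this: "A set of independent components will be identified as the common resting-state functional networks". Graph measures (efficiency, modularity, hubs) are computed, and "A dual regression approach will be used to investigate between-group differences in the individual functional networks". Voxel-wise tests use a 0.05 threshold with family-wise error correction.

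On acquisition, "resting-state fMRI of 150 T2-weighted gradient echo planar imaging (EPI) will be acquired with TR = 2 s". There are two scans per participant, one before and one after treatment. Staff monitor participants in the scanner, but no motion criterion is given.

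The Statistical analyses section has one covariate rule, and it covers only sociodemographic factors that differ significantly between the arms.

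Two of the Secondary hypotheses bear on this point. One expects a "30% improvement in both attention deficit and reduction in hyperactivity and impulsivity after 2 weeks of TPS treatment compared with the sham TPS group". The other states: "Participants in the verum TPS group will have more brain connectivity changes after 2 weeks of TPS compared with the sham TPS group". Connectivity change is also the third item under Objectives.

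**The concern.** Motion correction puts the volumes back into alignment. It does not remove the signal changes that movement causes, and these can alter the correlations between regions from which connectivity is estimated. That matters in any resting-state study, but this trial has a particular exposure. Its participants have ADHD, and the treatment is hypothesised to reduce hyperactivity. If it does, the verum adolescents may lie stiller than the sham adolescents at the second scan, which is the scan that carries the connectivity comparison.

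Such a difference would arise after randomisation and as a result of treatment, so randomisation does not balance it. Family-wise error correction limits chance findings across voxels; it does nothing about a systematic shift. The connectivity hypothesis names no network and no direction, so a motion-driven difference of either sign could be read as support. At stake is the interpretation of the third objective: on the plan as published, a positive result could not be told apart from stiller participants.

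**Working it through.** The article gives no figure for motion, so there is none to reproduce. The check has two parts.

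**1. What the text provides against motion**

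| Safeguard | Neuroimaging and Statistical analyses sections |
|---|---|
| Motion correction | Named |
| Removal of motion components | Not named; ICA is given one purpose, identifying networks |
| Motion covariate in the group comparison | Not named; the covariate rule is sociodemographic only |
| Scan-motion limit or rescan rule | Not named; monitoring during the scan only |
| Motion compared by arm or visit | Not named |

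Run length: 150 volumes × 2 s = 300 s = 5 min. In so short a run, a few movements affect a sizeable share of the data.

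**2. How large the error could be (illustration)**

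Inputs:
- n = 15 per arm, from the Sample size section, so df = 2 × 15 − 2 = 28.
- Two-sided level 0.05, critical t = 2.048.
- r, the within-arm correlation of motion change with the change in a connectivity measure: 0.3 to 0.5, assumed.
- d_m, the between-arm difference in motion change: 0.5 to 0.9 SD, assumed.
- No true connectivity effect.

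Spurious standardised difference: d_s = r × d_m. 
Non-centrality: δ = d_s × √(n/2) = d_s × √7.5 = 2.739 × d_s. 
False-positive rate: P(|T| > 2.048), with T non-central t on 28 df and non-centrality δ.

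| d_m | r | d_s | δ | Rate |
|---|---|---|---|---|
| 0 | any | 0 | 0 | 5.0% |
| 0.5 | 0.3 | 0.15 | 0.41 | 6.8% |
| 0.5 | 0.5 | 0.25 | 0.68 | 10.1% |
| 0.9 | 0.3 | 0.27 | 0.74 | 11.0% |
| 0.9 | 0.5 | 0.45 | 1.23 | 22.2% |

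The bias d_s does not depend on n, so a larger trial would not shrink it. The rates describe one uncorrected test, such as a single graph metric. They are not the error rate of the voxel-wise, family-wise-corrected dual regression.

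**The case against.** The strongest objection is that this is a condensed article. It leaves out other routine steps too, such as smoothing and temporal filtering, so silence about denoising does not show that none is planned. A fuller protocol or imaging manual may contain it. This stands as a limit on the claim. A reader might infer that motion is handled by realignment alone; the text says neither that nor that ICA will not also be used to separate noise. It does commit to a named sequence, detailed down to repetition time and error threshold, and that sequence followed as written has no means of separating artefact from effect.

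A reader might also infer that movement is bound to fall more under verum, or that parental expectancy would make it do so. The documents support neither. There are no motion data, and a lower hyperactivity rating need not mean less movement in the scanner. Parents and participants are blinded and a sham is used, so expectancy should be similar in both arms unless blinding fails.

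The size is open to challenge as well. Both inputs to the calculation are assumed, and 22% is the most extreme of the combinations shown.

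Finally, adjusting for motion conditions on a variable measured after randomisation. That can bias the comparison or remove a true effect, so adjustment should not decide whether a connectivity effect may be claimed.

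**Conclusion.** The point holds as a weakness of the published imaging analysis. It does not show that connectivity results will be false. A between-arm motion difference is a plausible rival explanation that follows from the trial's own hypothesis about hyperactivity, and the steps named cannot rule it out.

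The size is unknown. The range of about 7% to 22% rests wholly on the assumed r and d_m and on a single uncorrected test; if the arms do not differ in motion change, the rate stays at the nominal level. The consequence is confined to a secondary outcome, the third objective. It should be dealt with before unblinding because the remedy is cheap. If a fuller document already specifies denoising and a motion limit, stating them would settle most of the point.

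**What to change.** Keep the FSL pipeline and add the following:

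1. ICA-based removal of motion components before dual regression and before the graph metrics.
2. One limit on scan motion, fixed before unblinding and applied to all scans alike.
3. Mean framewise displacement reported by arm and visit.
4. A sensitivity analysis of the group comparison adjusted for the pre-to-post change in displacement. Report it beside the main result with the caveat that motion is a post-randomisation variable, and do not use it as a veto.

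The cost is a little analysis time, since displacement comes from the motion correction already planned. The downsides are the possible loss of a few scans, which at 15 per arm should be reported by arm, and the possible removal of some true signal that tracks motion.

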### Inclusion criteria

The inclusion criteria are as follows: (1) those who have a confirmed diagnosis of ADHD according to the 5th edition of the Diagnostic and Statistical Manual of Mental Disorders (DSM-5) of the American Psychiatric Association; (2) those with Chinese ethnicity, aged 12–17 years, with no co-morbidity of other mental disorders (e.g., intellectual disability disorders) or organic brain diseases that affect cognitive functions; (3) those who have no severe systemic diseases including heart, liver, lung, and kidney diseases; (4) those who have an IQ of >80 by Stanford–Binet Intelligence Scale, 5th Edition (SB-5); and (5) those who have written consent from parents.

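### The resting-state fMRI pipeline specifies linear registration to the template and names no nonlinear step before voxel-wise group tests, which can cost sensitivity to a focal effect

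*Protocol article*

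**What the plan says.** The Neuroimaging section sets out the functional connectivity analysis in order. The resting-state "volumes will be pre-processed, with motion correction and slice timing correction", and are "then linearly registered to the Montreal Neurological Institute (MNI) standard space". Independent component analysis follows. Then "A dual regression approach will be used to investigate between-group differences in the individual functional networks", with a family-wise-error-corrected level of 0.05: "The significance threshold of the voxel-wise differences will be set at". The same section also plans global and local efficiency, modularity and hubs as network summaries.

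On acquisition, the functional images have "32 slices, with a resolution of 3 × 3 × 4 mm". A structural scan is also taken: "High-resolution sagittal 3D T1-weighted (SPGR/MPRAGE) images of 1 × 1 × 1 mm will be acquired". Each participant is scanned twice: "Participants will receive pre- and post-treatment MRI scans (total: two MRI scans"). Under Inclusion criteria, the participants are "those with Chinese ethnicity, aged 12–17 years". The Sample size section sets 15 per group, 30 in all.

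Connectivity is the third item under Objectives and the last secondary hypothesis. The primary outcome is the parent-rated SNAP-IV.

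Neither the Neuroimaging nor the Statistical analyses section mentions a nonlinear registration step for the resting-state data, a smoothing kernel, an expected registration error, or an effect size or power for connectivity.

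**The concern.** The article does not leave registration open. It chooses a method, and the method is linear. A linear transform has only global terms (position, rotation, scale, shear), so two participants with differently shaped cortex can still have different tissue at the same template voxel. Dual regression yields one map per participant, but all maps lie on the same template grid, and the group test compares them voxel by voxel. Dual regression therefore does not undo the mismatch. Averaging over participants whose effects sit at slightly different voxels lowers and widens the group effect.

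This trial is exposed to that loss because it describes its stimulation as highly focal and aims it at one region, the left DLPFC (Mechanisms of TPS; Treatment region). A focal effect loses most from misalignment. With 15 per arm and family-wise correction, there is little sensitivity to give away. What is at stake is the chance of seeing a real local connectivity effect in a secondary outcome.

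**Working it through.** **No figure to reproduce.** The article states no registration error, smoothing kernel, effect extent or imaging power. The calculation below is an illustration under assumed values.

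**Inputs from the article.** 15 per arm and a standardised effect d = 0.91 (Sample size section). That effect comes from a depression trial and is borrowed here only to have a starting value.

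**Assumed inputs.** A Gaussian effect of given full width at half maximum (FWHM), and residual misalignment between participants with standard deviation s per axis, independent across three axes.

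**Formulas.** σ = FWHM / 2.355. The share of the peak kept in the group average is (σ² / (σ² + s²))^1.5. The diluted effect is d × that share. Power is that of a two-sample t-test with 28 degrees of freedom and noncentrality d × √7.5, two-sided 0.05, at a single voxel without family-wise correction.

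**Worked case, FWHM 10 mm.** σ = 10 / 2.355 = 4.25 mm, σ² = 18.0.
- s = 2 mm: (18.0 / 22.0)^1.5 = 0.74
- s = 3 mm: (18.0 / 27.0)^1.5 = 0.54
- s = 4 mm: (18.0 / 34.0)^1.5 = 0.39

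**Worked case, FWHM 20 mm.** σ = 8.49 mm, σ² = 72.1.
- s = 2 mm: (72.1 / 76.1)^1.5 = 0.92
- s = 4 mm: (72.1 / 88.1)^1.5 = 0.74

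Reducing misalignment from 4 to 2 mm would thus raise the peak by a factor of 0.74 / 0.39 = 1.9 for the 10 mm effect, but only 0.92 / 0.74 = 1.25 for the 20 mm effect.

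**Power over a wider grid.** Without misalignment, noncentrality is 0.91 × √7.5 = 2.49 and power is 0.67.

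| FWHM (mm) | s (mm) | Peak kept | Diluted d | Power |
|---|---|---|---|---|
| 8 | 1 | 0.88 | 0.80 | 0.57 |
| 8 | 2 | 0.64 | 0.58 | 0.34 |
| 8 | 4 | 0.27 | 0.25 | 0.10 |
| 12 | 1 | 0.94 | 0.86 | 0.62 |
| 12 | 2 | 0.81 | 0.73 | 0.49 |
| 12 | 4 | 0.49 | 0.44 | 0.22 |
| 16 | 1 | 0.97 | 0.88 | 0.64 |
| 16 | 2 | 0.88 | 0.80 | 0.57 |
| 16 | 4 | 0.64 | 0.58 | 0.34 |

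The direction is the same in every row: misalignment only lowers the peak. The size runs from trivial (0.67 to 0.64) to severe (0.67 to 0.10), and the article does not show which row applies. Family-wise correction would lower all these powers, including the 0.67.

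**Bias.** A participant's two scans share the same anatomy, so the mismatch is largely common to both. Allocation is randomised and the comparator is sham, so there is no reason for misalignment to differ between arms. With no treatment effect there is nothing to dilute, and the error rate is not raised.

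**The case against.** The strongest reply is that this is a condensed article. It gives no smoothing kernel, nuisance regression or number of components, and it plans voxel-based morphometry and fractional anisotropy maps without describing registration for either. Silence about a nonlinear step is weak evidence that none exists. This stands in part: a reader might infer that linear alignment is the only step performed, and the article does not say that. But the article states the registration step and calls it linear. If a warp is planned, the sentence still misdescribes the pipeline.

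The second reply concerns size, and it stands. A reader might infer that the networks will be poorly aligned, that a warp would nearly double the peak, or that a null map would be partly a registration artefact. The documents support none of these. The near-doubling needs a 10 mm focus and a reduction in misalignment from 4 to 2 mm; networks from independent component analysis need not be 10 mm foci, and nothing shows that a warp would achieve that reduction. The assumed errors are also about the size of the 3 × 3 × 4 mm acquisition voxel. A null map has other sufficient explanations: 15 per arm, a sample size not based on imaging, and family-wise correction. The size of any mismatch between 12- to 17-year-olds and the template is likewise not given.

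Third, it might be thought that the whole connectivity objective depends on this step. It does not: the planned efficiency, modularity and hub measures are network summaries, and the dilution calculation does not address them.

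**Conclusion.** The point holds as a low-cost improvement. The article specifies linear registration to template space, names no nonlinear step, and then tests voxel by voxel in 30 adolescents. Linear alignment leaves local anatomical differences uncorrected, which can dilute a focal effect and reduce sensitivity. The direction follows from the method. The size cannot be derived from the article; the illustration (27% to 97% of the peak kept) rests on assumed effect widths, assumed misalignment, a Gaussian shape and a borrowed effect size.

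The consequence is confined to the voxel-wise part of a secondary imaging outcome. The arm comparison stays unbiased, type I error is not inflated, and the SNAP-IV analysis is unaffected.

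**What to change.** Change the registration sentence in the Neuroimaging section so that each fMRI series is registered linearly to the participant's own T1 image, the T1 image is registered nonlinearly to MNI space, and the combined transform is applied once, before independent component analysis and dual regression. Add that every registration is checked visually by someone blind to arm. If the full imaging protocol already contains a nonlinear step, correct the sentence to say so.

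The cost is this change of wording, computing time, and a visual check of about 60 scans (30 participants × 2). No new scan, visit or participant is needed, because the 1 mm T1 image is already planned. The checks are a real burden, since a nonlinear warp can fail locally and has to be inspected.

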### Statistical analyses

All statistical analyses will be performed using the statistical software R for Windows (R version 4.1.0). Means and standard deviations (SD) for the continuous variables will be presented, while numbers and percentages for the categorical variables will be shown. A *p*-value of < 0.05 is considered statistically significant. Sociodemographic differences between the TPS group and the sham TPS group will be analyzed using the Chi-square test and *t*-test. If there are significant differences between sociodemographic factors, covariates will be considered confounding variables in the analyses. The normality of the primary outcome (SNAP-IV) scores will be tested by the Shapiro–Wilk test for each combination of factor levels (group and time). *T*-test will be used to test the baseline difference. A linear mixed model will be used to test the group (between-subject factor), time (within-subject factor), and group × time interaction effects of the SNAP-IV score between the TPS group and the sham TPS group. *Post-hoc* comparisons between groups and time points will be conducted using a *t*-test with Bonferroni correction. The normality of the secondary outcome scores will be tested by the Shapiro–Wilk test for each time point. For normally distributed outcomes, a linear mixed model will be used to determine whether the outcome scores are significantly different between the pre- and post-tests. For outcome scores that deviate grossly from normality, a non-parametric Friedman test will be used to test the mean difference. A Cohen's *d* effect size for each outcome will be calculated, where *d* = 0.2, 0.5, and 0.8 correspond to small, medium, and large effect sizes (54). Missing data will be managed by multiple imputations (55). For the neurological rs-fMRI data, a longitudinal voxel-based morphometry (VBM) will be used to examine whether TPS produces local changes in gray matter. Specifically, relative local increases and decreases between pre- and post-intervention scans will be compared within and between study groups. The diffusion MR data will be analyzed using the diffusion tensor model (56). Two standard diffusion indices will then be obtained: the apparent diffusion coefficient and the fractional anisotropy. Pre- and post-treatment DTI scans will permit the assessment of changes in axial diffusivity, with lower values being interpreted as the structural enhancement of white matter.

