**Methods:**

This study proposes a double-blinded, randomized, sham-controlled trial including TPS as an intervention group and a sham TPS group. Both groups will be measured at baseline (T1), immediately after the intervention (T2), and at the 1-month (T3) and 3-month follow-ups (T4).

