### Screening and self-administered questionnaire

Participants' parents will complete a QR code online application form soliciting sociodemographic information [age, gender, educational background, monthly family household income, living circumstances, school year, participant's psychiatric history, and duration of ADHD diagnosis (in years/months)], age of diagnosis, duration of taking prescribed medications (in years/months), current drugs and dosages, and family history of psychiatric disorder.

Eligible subjects will then fill in the screening tool (The Swanson, Nolan, and Pelham Rating Scale (SNAP IV), and those with a SNAP IV mean score of >2 will be recruited. Subjects' medical history, treatment regime, and developmental history will be obtained by direct inquiry with subjects' parents either by Zoom interview or Facetime before neuroimaging and TPS treatment. Both participants and parents will be interviewed by the PI and the research personnel. Parents need to hold a valid medical certificate of his/her child's ADHD diagnosis and a prescribed formulation sheet during the online interview. Any parent who fails to show this proof will not be invited to participate in the trial.

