### Randomization, allocation, and masking

All consenting participants will be listed in alphabetical order according to their surnames, and each participant will be assigned a unique identifier. An independent statistician ([name]) will use a computer-generated list of random numbers (www.random.org) to ensure the concealment of randomization. Randomization will be conducted by an independent statistician off-site using a stochastic minimization program to balance the gender, age, and SNAP-IV scores of the participants. Block randomization with blocks of 10 (total: 3 blocks) will be used to allocate treatment groups. Participants from each block will be randomly assigned to the verum TPS groups or the sham TPS groups on a 1:1 ratio. To avoid information flow, participants/parents and research associates will be blinded to the group allocation to minimize potential contamination of the effects of TPS or subject bias. The interventionist will not be involved in data collection or pre- and post-TPS measurements. Outcome measurements will be conducted by a research associate who is not involved in the group allocation. Participants and their parents will be asked to guess the grouping (verum TPS vs. sham TPS) in the last TPS session to determine the probability of guessing the group allocation correctly in the subject blinding (44).

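### Covariates are admitted only by a baseline significance test, and gender, age and baseline SNAP-IV are not prespecified covariates in the primary model

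*Protocol article*

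**What the plan says.** In the protocol article, under Statistical analyses, the arms are first compared at baseline: "Sociodemographic differences between the TPS group and the sham TPS group will be analyzed using the Chi-square test and" a t-test, with significance at p < 0.05. The consequence is then stated: "If there are significant differences between sociodemographic factors, covariates will be considered confounding variables in the analyses". A further t-test "will be used to test the baseline difference", with no stated consequence for the model.

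The primary analysis of SNAP-IV is given as: "A linear mixed model will be used to test the group (between-subject factor), time (within-subject factor), and group × time interaction effects". No covariate is named. Post-hoc comparisons between groups and time points are by t-test with Bonferroni correction.

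Under Randomization, allocation, and masking, an off-site statistician allocates "using a stochastic minimization program to balance the gender, age, and SNAP-IV scores of the participants". The next sentence describes a different method: "Block randomization with blocks of 10 (total: 3 blocks) will be used to allocate treatment groups".

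The screening section treats two of the balancing factors as sociodemographic ("soliciting sociodemographic information [age, gender, educational background" and further items), so age and gender can reach the model only through the significance rule. The abstract and the sample-size section make baseline (T1) one of four measurement times, with 15 subjects per group.

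**The concern.** When allocation is random, any baseline difference is due to chance. A baseline p-value therefore tests a hypothesis already known to be true. It does not show whether a variable is related to the outcome, and that relation is what makes adjustment worthwhile. The rule can fail in both directions: it passes over a moderate imbalance in a prognostic factor and admits a factor with no bearing on SNAP-IV. It also leaves the primary model open until the baseline data have been tested.

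The rule works against the balancing as well. The better age and gender are balanced, the less likely they are to be flagged and adjusted for. Yet if balancing factors are prognostic and are left out of the analysis, the reported standard error is too large. For baseline SNAP-IV, the question is whether a model with T1 as a response uses the baseline score well. At stake are precision in a trial of 30 and a primary model fixed in advance.

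**Working it through.** **Inputs.** From the sample-size section: 15 per group, significance level 0.05 (taken as two-sided, because sidedness is not stated), d = 0.91. Assumed: equal SDs over time and arms, and a T1–T2 SNAP-IV correlation ρ of 0.3 to 0.8. The document gives no ρ.

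**The plan's own figure.** The 15 per group for 95% power can be neither confirmed nor refuted. A simple two-sided t-test at d = 0.91 needs 33 per arm. A four-visit repeated-measures test of the group effect (f = d/2 = 0.455) needs 28 in total at ρ = 0.2, 32 at ρ = 0.3 and 42 at ρ = 0.5. The corresponding interaction test needs 12 at ρ = 0.5. This point does not depend on which was used.

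**1. What the baseline test can detect.**
- Continuous factor: the smallest flagged difference is t(0.975, 28) × √(2/15) = 2.048 × 0.365 = 0.75 SD. If the underlying difference were 0.5 SD, the test would flag it 26% of the time; at 0.3 SD, 12%.
- Gender, 10/15 v 5/15: χ² = 30 × (10×10 − 5×5)² / 15⁴ = 3.33, p = 0.07, not flagged. 10/15 v 4/15 is flagged only without continuity correction. 10/15 v 3/15 is flagged either way.

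**2. Chance of a false flag.** The rule does not list its factors. Treating tests as independent at 5% each:
- all eight items under Demographic data: 1 − 0.95⁸ = 34%;
- without age and gender, which may be minimised: 1 − 0.95⁶ = 26%;
- also without BMI, birth history and family history of ADHD, which are not plainly sociodemographic: 1 − 0.95³ = 14%.

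**3. What each SNAP-IV analysis does with a chance baseline difference.** The table gives the expected shift in the estimate per 1 SD of T1 difference. A simulation of 40,000 trials with equal correlation between visits agrees with the formulas to about 0.01.

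| Analysis | Formula | ρ = 0.5 | ρ = 0.7 |
|---|---|---|---|
| Between-group comparison at T2 alone | ρ | +0.50 | +0.70 |
| Group × time contrast, T2 minus T1 | ρ − 1 | −0.50 | −0.30 |
| Group effect averaged over T1–T4 | (1 + 3ρ)/4 | +0.63 | +0.78 |
| T2 adjusted for baseline | 0 | 0 | 0 |

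The interaction contrast over-corrects. The group main effect and a plain between-group t-test at follow-up do not correct.

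**4. Precision and power at T2.** Relative variance is 2(1 − ρ) for the change contrast and 1 − ρ² for the adjusted contrast, so their ratio is 2/(1 + ρ). Power is from the noncentral t with 28 df and noncentrality 0.91 × √(15/2) / √variance.

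| ρ | Change | Adjusted | Excess variance of change | Power, change to adjusted |
|---|---|---|---|---|
| 0.3 | 1.40 | 0.91 | 54% | 53% to 71% |
| 0.5 | 1.00 | 0.75 | 33% | 67% to 79% |
| 0.7 | 0.60 | 0.51 | 18% | 87% to 92% |
| 0.8 | 0.40 | 0.36 | 11% | 97% to 98% |

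**5. Cost in degrees of freedom.** At ρ = 0.5, adjusted power is 79.3% with 28 df, 79.2% with 27 and 79.0% with 25.

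**The case against.** The strongest reply is that baseline SNAP-IV is already in the model. A reader might infer that SNAP-IV imbalance goes uncorrected in the primary analysis, but the document does not support that. T1 is one of the four responses, and the group × time contrast subtracts it. This reply stands. What remains is that subtraction over-corrects and is less precise than adjustment. Lack of correction applies only to the group main effect and to between-group t-tests at follow-up.

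The size is also uncertain. The power gain runs from about 18 points at ρ = 0.3 to about 1 point at ρ = 0.8, so no single figure describes the loss. The variances are for one T2 contrast, not the joint test over four visits, and they assume that SNAP-IV balance is left to chance. No gain can be shown for age and gender, because the document gives no association between either and SNAP-IV.

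The balancing argument depends on the minimisation sentence. The blocks of 10, with no strata named, would not balance these factors. If blocks alone are used, the argument about too large a standard error falls away, but chance imbalance is then more likely and prespecified adjustment helps for that reason. Under effective minimisation, a large SNAP-IV imbalance would be unlikely.

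Keeping T1 as a response is a recognised approach, so requiring a baseline covariate would be partly preference. The fix therefore allows either form.

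Leaving detail to a separate analysis plan is no defence here: the article states a covariate rule, and the rule is unsound.

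**Conclusion.** The point holds. The significance-triggered rule should not decide the model: at 15 per arm it ignores continuous imbalances below about 0.75 SD and a gender split of 10/15 v 5/15. It has perhaps a 14% to 34% chance of admitting at least one factor by chance, depending on which factors are tested and if the tests are independent. The factors named for minimisation are not fixed covariates in the stated primary model.

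For baseline SNAP-IV the fault is inefficient use, not omission. Adjustment was better at every correlation tried, with an 11% to 54% variance excess for the change contrast over assumed ρ of 0.8 to 0.3. The direction holds for any ρ below 1, because 2/(1 + ρ) is then above 1; the amount rests on the assumed ρ. The trial remains interpretable, so this should be corrected but does not invalidate the design.

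**What to change.** Delete the significance-triggered covariate rule and the baseline t-test, and describe baseline characteristics without p-values.

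Prespecify the SNAP-IV mixed model in one of two forms:
- T2 to T4 as outcomes, with baseline SNAP-IV, age and gender as fixed covariates; or
- T1 to T4 as outcomes with the arm means constrained equal at T1, plus age and gender.

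Take the between-group comparisons at each follow-up visit from this model instead of from separate unadjusted t-tests.

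For secondary outcomes analysed by mixed model, adjust for the outcome's own baseline where one exists. CGI-I rates change from baseline and so has no baseline value; use a suitable baseline measure such as CGI-S.

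The cost is wording and two or three degrees of freedom. Going from 27 to 25 df takes about 0.2 points of power at ρ = 0.5. All the variables are already collected, and no extra participants are needed.
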